## Abstract

**Background:**

It is estimated that approximately 50% of stroke survivors will experience swallowing difficulty, or dysphagia. The associated sequelae of dysphagia include dehydration, malnutrition, and aspiration pneumonia, all of which have can have serious medical consequences. To improve swallowing safety and efficiency, alternative nutritional intake methods (for example, a feeding tube) or a modified diet texture (such as pureed foods or thickened liquids) may be recommended but these modifications may negatively affect quality of life. An alternative approach to treating dysphagia has emerged over the past few years, targeting stronger lingual muscles through maximal isometric pressure tasks. Although these studies have shown promising results, thin-liquid bolus control continues to be challenging for patients with dysphagia. Previous work investigating lingual pressures when healthy participants swallow has suggested that greater task specificity in lingual exercises may yield improved results with thin liquids.

**Methods/design:**

This is a small, exploratory randomized clinical trial being conducted with post-stroke patients 4 to 20 weeks after onset of dysphagia secondary to impaired lingual control. At enrollment, participants are randomly assigned to one of two treatment protocols, either tongue pressure profile training (TPPT) or the control treatment, tongue pressure strength-and-accuracy training (TPSAT). Each treatment protocol consists of 24 sessions of treatment over 8 to 12 weeks with monitoring of tongue pressure as well as a baseline and outcome videofluoroscopic swallowing study. Tongue pressure measures, videofluoroscopic measures, and functional outcome measures will be obtained following training of 60 participants (30 in each condition), to determine whether TPPT yields better outcomes.

**Discussion:**

This study will continue to explore options beyond tube feeding and modified diets for people with neurogenic dysphagia following stroke. Should the novel protocol, TPPT, prove to be more effective than the TPSAT protocol, this may influence standards of care and best practices for patients with dysphagia involving impaired thin-liquid control as a result of stroke.

**Trial registration:**

Clinicaltrials.gov http://NCT01370083NCT01370083

## Background

Drinking thin liquids is something that most of us take for granted, yet this task is one that many patients with dysphagia (swallowing impairment) cannot do safely. Instead, these individuals receive liquids in thickened form: thickened juice, thickened coffee, and even thickened water [1]. The literature tells us that patients dislike the taste and feel of thickened liquids and find that their thirst is not quenched. Patients on a diet with thickened liquids are prone to inadequate fluid intake and dehydration [2,3]. Many patients are noncompliant and drink thin liquids, despite documented risk of aspiration (that is, airway invasion) and its consequences [4]. Given these limitations, it is important that dysphagia researchers continue to pursue treatments with the potential to restore safe and functional thin-liquid swallowing in people with dysphagia.

In the past decade, tongue pressure resistance training has emerged as an innovative treatment for dysphagia. Robbins has shown that 8 weeks of intensive tongue pressure resistance training improves tongue strength in healthy seniors and those with both chronic and acute dysphagia following stroke [5,6]. In these studies, she had the participants complete an 8-week tongue-strengthening training protocol with an Iowa oral performance instrument (IOPI). Her findings included significantly improved isometric tongue pressures and swallowing pressures in all of the three populations that she studied (healthy participants, acute dysphagia, and chronic dysphagia). Although significant gains were made in airway protection, as judged by reduced scores on the penetration-aspiration scale [7], it is of ongoing concern that people with dysphagia after a stroke often have difficulty controlling the flow of thin liquids. Early arrival of a liquid bolus in the pharynx, secondary to poor oral control, represents a risk of penetration-aspiration (entry of material into the airway) [8].

Prior case series studies [9-11] have shown that patients who have completed a tongue pressure strength-and-accuracy resistance training protocol (TPSAT) showed improvements in tongue strength and aspiration. However, participants in these studies were not specifically recruited based on evidence of impaired liquid flow control, so the impact of the protocol on this feature could not be clearly elucidated. An analysis of patients treated to date in our lab suggests that approximately 30% of participants who complete the TPSAT protocol experience functional improvements in swallow response time for thin-liquid swallows. We speculate that strength-focused tongue pressure resistance tasks might lack sufficient task specificity to target improved liquid flow-control outcomes directly. We think that tongue pressure resistance training protocols would yield improved swallowing outcomes if they were modified to focus on tasks with similar pressure profiles (strength and timing) to those seen in healthy liquid swallowing.

To investigate this hypothesis, we have completed a study of tongue pressures (strength and timing) in healthy people, which shows that tongue pressures are released more slowly with thin liquids than with thick liquids [12]. This finding reveals active control of thin-liquid flow, and suggests that both the strength and timing of tongue pressure play a role in flow control. We believe that treatment outcomes would be better if tongue pressure resistance training protocols take both strength and timing into consideration. To this end, we have recently identified a subset of tongue pressure training tasks for which the strength and timing profile of tongue pressure onset and release is similar to that seen in liquid swallowing in healthy individuals [13]. We hypothesize that a treatment protocol will have better potential to yield favorable outcomes for thin-liquid flow control if it focuses on such tasks.

## Methods/design

### Study objectives

The primary objective of this study is to explore whether tongue pressure resistance training can be used to improve impairments in thin-liquid flow control for individuals with neurogenic dysphagia. To measure thin-liquid flow control, we will calculate the duration that a thin liquid is located in the pharynx prior to the onset of hyolaryngeal movement for airway protection; this measure is also known as the swallow response time [8]. Swallow response times in aspirating stroke patients have recently been reported to be significantly longer (620 ms ± standard error of 160 ms) than those seen in nonaspirating patients (20 ms ± 100 ms) [8]. In this study, we want to determine whether TPPT, which addresses both timing and amplitude issues in tongue pressure generation, yields better functional outcomes with respect to swallow response time than strength-and-accuracy focused treatment. The ultimate goal of this work is to develop interventions that restore functional swallowing ability in individuals who are unable to swallow thin liquids safely.

### Study design

This study is a small, exploratory randomized trial comparing treatment outcomes for two tongue pressure resistance training protocols: TPPT focuses on tongue pressure strength and timing, whereas TPSAT emphasizes target accuracy during strength tasks. Both protocols build on recent tongue pressure resistance training studies, which emphasized load and intensity, and are informed by physiological principles of muscle training through exercise.

Each training protocol consists of 24 intervention sessions, in addition to a baseline measurement session, a baseline videofluoroscopic swallowing study (VFSS), and an outcome VFSS. The VFSS outcomes will be measured using a series of three teaspoon-sized boluses of thin-liquid barium (Liquid Polibar diluted with water to a 22% w/v concentration).

Each training program will be delivered as two or three sessions per week on nonconsecutive days, commencing directly after enrollment. The outlines of the TPPT and TPSAT sessions are illustrated in Figures 1 and 2, respectively. Tongue-palate pressure tasks are performed with the IOPI bulb placed in both an anterior position (that is, with the flat end of the bulb positioned immediately behind the upper incisors) and a posterior position (that is, with the flat end of the bulb lined up with the first molar tooth). Although the tasks vary between the two protocols, the total number of exercise repetitions is held constant between the two protocols at 60 exercises per session. For the slow pressure release tasks in the TPPT protocol, the instruction is for the participant to release pressure gradually from a peak to a resting value, spanning at least a 3-second interval. The bolus-swallowing tasks included in the TPPT protocol involve a series of five discrete swallows, each 5 ml in volume, of the thinnest liquid consistency (either thin, nectar- or honey-thick liquid) that can be safely tolerated by the patient, as determined by the intake VFSS examination. A rest period of at least 30 seconds is provided between each swallow.

**Figure 1 F1:**
[figure not shown]
Outline of a tongue pressure profile training session.

**Figure 2 F2:**
[figure not shown]
Outline of a tongue pressure strength-and-accuracy training session.

With the exception of the bolus trials in the TPPT protocol, all tasks are performed using an IOPI. We have developed a computer interface that displays the IOPI waveform in real time on a computer-displayed graph to give visual biofeedback to the participant for all tasks.

All enrollment procedures, screening and training sessions will be conducted by a registered speech-language pathologist or a support worker (for example, a Communicative Disorders Assistant) under the direct or indirect supervision of a speech-language pathologist. All VFSS assessments will be conducted by a speech-language pathologist in conjunction with a radiation technologist.

### Study sites

This study is being conducted in two publicly funded rehabilitation centers in Ontario, Canada: the Toronto Rehabilitation Institute –University Health Network and the Kitchener-Waterloo Local Health Integration Network #3. Each of these settings has a neurorehabilitation program that provides inpatient and outpatient services.

### Ethical approval

This research protocol was reviewed and approved by the Toronto Rehabilitation Institute Research Ethics Board (#10-027), and the Tri-Hospital Research Ethics Board for Cambridge Memorial Hospital, Grand River Hospital and St. Mary’s General Hospital (#2012-0474).

### Study population

The participants enrolled in this study will have a primary diagnosis of stroke, as well as dysphagia presenting with prolonged swallow response time for thin liquids. Impaired swallow response time will be operationally defined as the presence of thin liquid in the pharynx (that is, below the shadow of the ramus of the mandible) for >350 ms prior to the onset of hyolaryngeal excursion. This threshold value falls halfway between the reported 95% confidence intervals for non-aspirating and aspirating stroke patients in a recent study [8]. We will measure this parameter on 5 ml swallows of thin-liquid barium using a cued swallow instruction. Participants must be patients (inpatient or outpatient) in one of the two participating rehabilitation settings to be enrolled in the study. Additional inclusion and exclusion criteria are detailed.

#### Inclusion criteria

To be included in the study, each participant must be able to understand English, be able to follow directions, and be able to tolerate oral trials under the supervision of a therapist. This is likely to exclude individuals with brainstem strokes, for whom swallowing is often profoundly impaired and oral trials are often unsafe. Additionally, to control for spontaneous recovery, enrollment into the study must occur at least four weeks after dysphagia onset and not more than 20 weeks following dysphagia onset. Within this enrollment window, a VFSS must be completed and recorded. The VFSS recording will then be scored by a speech-language pathologist to determine whether poor bolus control is present, as indicated by swallow response times >350 ms on teaspoon-sized volumes of thin-liquid barium. This will confirm eligibility to participate.

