### Randomization

During the intake procedure, participants will be randomly assigned to either the TPPT or TPSAT treatment conditions using a sequence generated by http://www.randomizer.org. Randomization will be concealed using sequentially numbered, opaque sealed envelopes.

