### Sample-size calculation

Our prior study of treatment outcomes from the TPSAT suggests that one-third of patients in the control group are likely to exhibit improvement in the primary outcome variable (average swallow response time above vs. below 350 ms). A sample-size calculation was conducted using Study Size Software 2.0, modeling the expectation (in a 2 × 2 contingency table) that the TPPT treatment will yield a greater rate of improvement, that is, in at least 66% of participants, than the current 30% response rate seen in cases accrued in our lab in historical studies. Under these assumptions, a sample-size calculation shows that 29 participants per group are needed to demonstrate a significant difference in rate of improvement at a *P* value of 0.05 and a power of 0.8. Therefore, we have established a targeted sample size of 60 participants (30 participants per protocol).

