### Data processing and analysis

The proposed analysis of differences in pressure measures will be a 2 (group) × 3 (task) × 2 (measurement point) repeated measures mixed-model analysis of variance. We will perform this analysis using SPSS’s mixed modeling procedure, which will allow us to model the covariance structure of the data accurately.

From the VFSS measures, the primary measure of interest will be a binary reduction of the participant’s mean swallow response time measure (less than or more than 350 ms). We will also record whether or not the participant’s worst penetration-aspiration scale score across the series of three teaspoon-sized boluses of thin-liquid barium is less than or more than 3, representing material remaining above and inside or below the supraglottic space, respectively, as the measure of swallowing safety. Two-by-two tables with chi-square tests will be used to test for differences in the proportion of participants in each treatment group with impaired versus normal swallow response time at the post-treatment VFSS, and also the proportion in each group who display impaired swallowing safety. Odds ratios for reduction in swallow response time and improved swallowing safety will be computed.

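### The primary chi-square test ignores time since dysphagia onset, which the protocol links to spontaneous recovery and needs for eligibility; the cost is forgone precision, not bias

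*Protocol article*

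**What the plan says.** The Inclusion criteria section of the protocol article sets the lower bound of the enrolment window and its purpose: "to control for spontaneous recovery, enrollment into the study must occur at least four weeks after dysphagia onset". The upper bound for entry is week 20. Each site therefore has to establish time since onset before a participant can enter.

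Time since onset is not mentioned again after eligibility. The Data processing and analysis section reduces the primary outcome to mean swallow response time below or above 350 ms at the post-treatment videofluoroscopy, and states the test: "Two-by-two tables with chi-square tests will be used to test for differences in the proportion of participants in each treatment group". No covariate or stratification factor enters that comparison.

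The Sample-size calculation section plans for improvement "in at least 66% of participants, than the current 30% response rate seen in cases accrued in our lab", with 29 per group needed and 30 planned.

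**The concern.** A window restricts time since onset; it does not account for what varies inside it. The latest entrant may be five times as far from onset as the earliest (20/4). Entry requires a swallow response time above 350 ms and success means a mean below 350 ms, so natural recovery alone can turn a participant into a success in either arm. If recovery still depends on time since onset within the window, two things follow for a trial of 60 people. Variation that could be explained stays in the error term, and an uneven mix of early and late entrants moves the observed difference without the test correcting for it. The planned size leaves one participant per group above the calculated need, so precision available at no data cost is worth having.

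**Working it through.** **Inputs from the protocol article.** Window 4 to 20 weeks; training 8 to 12 weeks, starting directly after enrolment; 30 per arm; 30% versus 66%; P 0.05; power 0.8.

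**Assumptions, not in the documents.** Half of participants enter early and half late; the success gap between early and late entrants is 0 to 40 points and is the same in both arms.

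**1. The plan's own figure.** Two-sided chi-square with pooled variance, mean proportion (0.30 + 0.66)/2 = 0.48:

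n = [1.96·√(2·0.48·0.52) + 0.842·√(0.30·0.70 + 0.66·0.34)]² / 0.36² = 29.03 per group.

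The stated 29 is reproduced. Exact power of the uncorrected chi-square test at 30 per arm is 0.82. (The same section also says "one-third of patients in the control group are likely to exhibit improvement in the primary outcome variable"; that inconsistency is a separate matter, and the 30% figure is used here.)

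**2. Timing of the outcome.** Entry at week 4 gives an outcome at about weeks 4 + 8 = 12 to 4 + 12 = 16. Entry at week 20 gives weeks 20 + 8 = 28 to 20 + 12 = 32.

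**3. Chance imbalance, taking 30:30 allocation without regard to time since onset.**
- With 30 early and 30 late entrants, the hypergeometric probability of an 18:12 split of the early entrants or worse is 0.196 (0.098 in each direction).
- If entry is instead uniform over the window, SD = 16/√12 = 4.6 weeks and the SE of the difference in arm means is 4.6·√(2/30) = 1.19 weeks, a 95% range of about ±2.3 weeks.

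**4. Size of the resulting shift.** An 18:12 split moves the observed difference by (18 − 12)/30 × gap = 0.2 × gap, which is 4, 6 or 8 points for gaps of 20, 30 or 40. The SE of the unadjusted difference is √(0.30·0.70/30 + 0.66·0.34/30) = 12.0 points, so 6 points is half of one SE.

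**5. What stratification recovers.** With gap g, the variance within strata in each arm is p(1 − p) − g²/4, so SE = √[(0.4344 − g²/2)/30]. Power is from simulation (200,000 trials per row, Mantel-Haenszel test without continuity correction).

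| Gap (points) | Control early/late | TPPT early/late | SE within strata (points) | Power, plain chi-square | Power, Mantel-Haenszel |
|---|---|---|---|---|---|
| 0 | 30/30% | 66/66% | 12.0 | 0.82 | 0.813 |
| 10 | 35/25% | 71/61% | 12.0 | 0.82 | 0.816 |
| 20 | 40/20% | 76/56% | 11.8 | 0.82 | 0.829 |
| 30 | 45/15% | 81/51% | 11.4 | 0.82 | 0.853 |
| 40 | 50/10% | 86/46% | 10.9 | 0.82 | 0.886 |

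Type I error of both tests was 0.048 to 0.053 at every gap. The Mantel-Haenszel gain requires the uncorrected statistic: with the usual 0.5 correction, power in the five rows is 0.73, 0.73, 0.75, 0.77 and 0.81.

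**6. Cross-check with continuous time.** With uniform entry and a logistic model with weeks since onset (3,000 trials per setting), unadjusted versus adjusted power was 0.83 v 0.83 with no time effect. It was 0.82 v 0.83, 0.82 v 0.84 and 0.82 v 0.87 when control success ran from 41% at week 4 to 20% at week 20, from 52% to 13%, and from 62% to 8%. Type I error of the adjusted likelihood-ratio test was 5 to 6%.

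**The case against.** Restriction is a recognised way to control a factor, and it is not the only one here. Entry also requires impairment still present on a videofluoroscopy within the window, and there is a concurrent randomised comparator. All of that stands.

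It rules out several stronger readings that a reader might draw:
- **That recovery biases the comparison or inflates type I error.** It does neither. Randomisation balances time since onset on average, and simulated error rates are near 5%.
- **That the trial misses its planned power.** It does not. Chance imbalance is already part of the 12-point SE, and plain power stays at 0.82 whatever the gap.
- **That allocation was unstratified.** The Randomization section says only that "participants will be randomly assigned to either the TPPT or TPSAT treatment conditions using a sequence generated by" a website and concealed in numbered envelopes. A condensed article need not say whether the lists were blocked, stratified or kept by site, so nothing can be concluded either way. If the lists were stratified on time since onset, the imbalance in step 3 would be smaller, but the plain chi-square would still not use the variable.
- **That training which ends before week 20 contradicts the protocol.** Twenty weeks is a limit on enrolment; the article never says recovery stops there.

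The other strong objection is that the benefit rests on a gradient the documents do not give. That is correct. At gaps of 0 to 10 points the stratified test is very slightly worse, and the larger gains need control success as far apart as 50% and 10%. The trial also describes itself as small and exploratory. What survives is narrower: the protocol itself names time since onset as relevant to recovery, must establish it for every participant, and then states outright a primary test that leaves it out.

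**Conclusion.** The point holds as a minor, inexpensive improvement to the stated analysis. The window limits spontaneous recovery but leaves a 16-week spread that the primary test does not use. The consequence is forgone precision and uncorrected chance imbalance.

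On the assumed half-and-half mix with a common gap in both arms, the gain in power at 30% versus 66% is about 1, 3 or 7 points for gaps of 20, 30 or 40 points. The loss is under 1 point if the gap is 0 to 10. The continuous-time check gives 0 to about 5 points. These figures depend on a recovery gradient that the documents do not supply. The absence of time since onset from the stated test does not.

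**What to change.** 1. **Data processing and analysis.** Keep the binary 350 ms endpoint and show the 2 × 2 table. Make the primary test a Mantel-Haenszel test, without continuity correction, stratified by early or late entry with the cut fixed before outcomes are compared by arm (for example 4 to 12 versus more than 12 to 20 weeks, the midpoint of the window). A logistic model with weeks since onset is an acceptable alternative; choose one in advance. Report the stratified or adjusted odds ratio beside the unadjusted one, because the two estimate slightly different quantities.
2. **Inclusion criteria.** Say that the window limits spontaneous recovery, and that the primary comparison takes account of the remaining spread in time since onset.

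No change to the randomisation is proposed.

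The cost is a short amendment and one extra term in the analysis. Time since onset is already needed for eligibility, so there are no new data and no new participants, and people already randomised are covered. The statistical price is the loss of less than 1 point of power if recovery turns out hardly to depend on time since onset.

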### Blinding

It is not possible to blind the participants or treating clinicians to the condition given the protocol differences in the two arms of the trial. All data analysis, including treatment outcome, will be blinded. For VFSS rating, individual swallow clips for the first three teaspoon-sized boluses of 22% w/v thin-liquid barium will be spliced from the recordings for each participant, and arranged in a randomized order in a master rating set. Two blinded speech-language pathologists will review and rate these recordings.

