### Outcome measures

Three types of data will be collected in this study: tongue pressure parameters, measures of swallow response time from videofluoroscopy, and measures of swallowing safety from videofluoroscopy. We will collect baseline and post-treatment pressure parameters (amplitude, duration, and slope) for the rise and release phases of tongue pressure events during three reference tasks (non-effortful saliva swallows, effortful saliva swallows, and posterior maximum isometric pressure tasks).

Videofluoroscopic measures will be collected at baseline and after treatment using a standardized videofluoroscopy protocol recorded on a KayPentax Digital Swallow Workstation at 30 frames per second. Two parameters will be rated for each spliced 5 ml thin-liquid barium (22% w/v) swallow:

1. Swallow response time (that is, the time difference between the arrival of the bolus head at the mandibular ramus and the onset of hyolaryngeal excursion, calculated in milliseconds, based on the time code of the video recording.

2. A measure on the eight-point penetration-aspiration scale [7], which determines the severity of and response to entry of the bolus into the airway.

The primary outcome variable of interest will be a measure of the participant’s average swallow response time across a series of three thin-liquid swallows (each 5 ml in volume). The targeted outcome will be an average swallow response time value shorter than 350 ms.

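### The entry rule does not say how swallows are combined at 350 ms, while success is a post-treatment three-swallow mean below 350 ms, so success need not mean improvement

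*Protocol article*

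**What the plan says.** **Entry.** Under Study population, impairment is thin liquid in the pharynx "for >350 ms prior to the onset of hyolaryngeal excursion", measured on 5 ml swallows. Under Inclusion criteria, "The VFSS recording will then be scored by a speech-language pathologist to determine whether poor bolus control is present", and the criterion is that "poor bolus control is present, as indicated by swallow response times >350 ms on teaspoon-sized volumes of thin-liquid barium". Neither section gives a number of swallows or a rule for combining them.

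**Outcome.** Under Outcome measures, the primary variable is the participant's "average swallow response time across a series of three thin-liquid swallows", and "The targeted outcome will be an average swallow response time value shorter than 350 ms". Videofluoroscopic measures are taken at baseline and after treatment. Under Blinding, clips of the first three teaspoon boluses are put in random order and "Two blinded speech-language pathologists will review and rate these recordings".

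**Test.** Under Data processing and analysis, a 2 × 2 chi-square compares the arms on "impaired versus normal swallow response time at the post-treatment VFSS". Baseline status does not enter. The same section promises an odds ratio for reduction in swallow response time, and Sample-size calculation speaks of a rate of improvement.

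**The concern.** Post-treatment status equals improvement only if everyone starts impaired on the scale used to judge success. Entry and outcome share the 350 ms cut, but only the outcome says what is compared with it. If some entrants already have a three-swallow mean below 350 ms, they are scored as successes in either arm with no change. That raises both success rates, shrinks the difference between them, and gives an odds ratio labelled as reduction that partly reflects status at entry. The planned sample leaves little slack, because the stated 29 per group gives almost exactly the 80% power aimed for.

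**Working it through.** **1. Can the case occur?** Take baseline times of 500, 250 and 200 ms. One swallow exceeds 350 ms and the mean is 950/3 = 317 ms. With 400, 400 and 200 ms, two exceed it and the mean is 1000/3 = 333 ms. Whether either person enters depends on a rule the text does not give. If every swallow, or the mean, must exceed 350 ms, neither enters, and on the same reader's figures no entrant can have a mean below the cut.

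**2. The plan's sample size.** Inputs from Sample-size calculation: 0.30 v 0.66, alpha 0.05 (taken as two-sided), power 0.80. With pooled proportion 0.48,

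n = [1.96·√(2·0.48·0.52) + 0.842·√(0.30·0.70 + 0.66·0.34)]² / 0.36² = (1.385 + 0.555)² / 0.1296 ≈ 29.0.

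The stated 29 is reproduced (30 when rounded up; the arcsine formula gives 29).

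**3. Share of entrants already below the cut (assumptions).** The documents give no between-patient or per-swallow standard deviation. I simulated 400,000 patients per setting. Each has a normally distributed true time and three swallows with normal error. I then took the share of entrants with a baseline mean of 350 ms or less.

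| Assumed mean; between-patient SD; per-swallow SD (ms) | Any swallow >350 | Two of three | All, or mean |
|---|---|---|---|
| 320–450; 250–300; 150–300 (four sets) | 19–33% | 4–8% | 0% |
| 620; 250–300; 150–250 | 9–13% | 2–3% | 0% |

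The 620 ms is the figure reported for aspirating stroke patients under Study objectives. A wider grid (mean 350–620 ms, per-swallow SD 100–300 ms) gives 7–35% for any swallow and 1–10% for two of three.

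**4. Effect on power.** Suppose a share f of each arm is below 350 ms regardless and the rest respond as planned. The rates become 0.30(1 − f) + f and 0.66(1 − f) + f. With 30 per group, power = Φ[(d − 1.96·SE₀)/SE₁], where d is the difference in rates, SE₀ uses the pooled proportion and SE₁ the separate ones.

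- At f = 0: (0.360 − 1.96·0.1290)/0.1203 = 0.89, so power is 0.81.
- At f = 0.20: (0.288 − 1.96·0.1273)/0.1217 = 0.32, so power is 0.62.

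| f | Control v TPPT | Odds ratio | n per group for 80% | Power at 30 per group |
|---|---|---|---|---|
| 0 | 0.300 v 0.660 | 4.5 | 30 | 0.81 |
| 5% | 0.335 v 0.677 | 4.2 | 33 | 0.77 |
| 10% | 0.370 v 0.694 | 3.9 | 37 | 0.72 |
| 20% | 0.440 v 0.728 | 3.4 | 45 | 0.62 |

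**The case against.** **The text is silent rather than wrong.** The criterion speaks of swallow times in the plural, and how screening swallows are combined is a detail that a condensed article may leave to the full protocol. This largely stands: the entry wording alone would be little more than a request for clarification. What remains is in the article itself. It fixes a primary test on post-treatment status, describes the result as improvement and reduction, and leaves out of that test the baseline measure it collects. A reader might infer that the plan admits patients on a single long swallow. The text does not say so; it only fails to exclude it.

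**The larger figures need the most permissive reading.** This stands. The 19–33% range needs any-swallow entry and a population centred near the cut, and the standard deviations are assumed throughout. A fall in power from 0.81 to 0.62 is an illustration at f = 20%, not a consequence of the plan.

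**The loss may be counted twice.** The plan contrasts TPPT with a rate higher "than the current 30% response rate seen in cases accrued in our lab". If those historical cases included participants who were normal at baseline, the 30% already contains them. The documents do not settle this.

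**A reader might infer bias toward one arm, from regression to the mean or from entry being read by one clinician.** The documents do not support that. Eligibility is confirmed on the baseline recording, before any treatment effect can appear, and allocation is random and concealed. Both effects therefore fall equally on the arms in expectation. Regression to the mean is handled by the concurrent control. Mean-based entry would not remove it: in the four settings centred near the cut, 11–23% of such entrants still retest below 350 ms with no true change.

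**Conclusion.** The point holds in limited form. As written, entry does not guarantee impairment on the outcome's own scale. The primary test ignores baseline, so neither the test nor its odds ratio need measure improvement. The affected share is unknown: under the assumed variances it is 0% if all swallows or the mean must exceed 350 ms, about 2–8% for two of three, and about 9–33% for any swallow. If such participants stay normal and are not already inside the 30%, even a 5% share takes power at 30 per group below the planned 0.80. The consequence is dilution and a mislabelled estimate, not a false advantage for either treatment.

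**What to change.** 1. State the entry criterion as a mean swallow response time above 350 ms over the three 5 ml thin-liquid swallows.
2. Analyse the primary binary outcome by logistic regression on treatment with the blinded baseline mean swallow response time as covariate. Keep the chi-square as supportive.
3. Pre-specify a sensitivity analysis restricted to participants whose blinded baseline mean exceeds 350 ms, so that reduction means a change from impaired to normal. This also covers patients enrolled before the clarification, and any difference between the screening reading and the blinded one.

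**Cost.** No new procedure is needed, since baseline swallows are already recorded and rated. The model is slightly more complex, and its odds ratio is conditional on baseline, so it will not equal the one from the 2 × 2 table. Enrolment is in progress, so a few borderline patients may become ineligible part-way through. Record which entry rule applied to each participant. The gain in power from the covariate depends on how strongly baseline predicts outcome, which the documents do not give.
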